### Outcomes

#### Baseline assessment

The surgical duration of the MSFE procedure will be calculated from the time of the initial incision to the end of wound closure. CBCT will be performed before and immediately after the MSFE procedure. Periapical images will be obtained as soon as the crowns are placed. These digital radiographic data will be used as the baseline radiographic data. Patients will be asked to score their discomfort (i.e., pain and edema levels) immediately and 2 weeks after surgery using a visual analog scale (VAS). The condition of the mucosa will be assessed at 6 months as the baseline clinical outcome.

#### Bone biopsy and histological/histomorphometric analyses

After an osteogenesis period of 6 months, histological and histomorphometric analyses will be performed of biopsy samples retrieved from the grafting sites. The bone biopsy samples will be collected during dental implant surgery with the use of a hollow trephine drill, fixated in 10% formaldehyde (pH 7.4; 4 °C), transferred to 70% ethanol, and stored until used for histomorphometric analysis. The samples will be subsequently dehydrated in descending concentrations of ethanol, embedded in low temperature polymerizing methyl methacrylate, sectioned (thickness, 4 μm), and stained with both hematoxylin-eosin and modified Mallory aniline blue. The sections will be divided into regions of interest (ROI). For each ROI, histomorphometric measurements will be performed blindly. The bone volume, graft volume, osteoid volume, and connective tissue volume will be calculated as a percentage of the total tissue volume. The osteoid-graft perimeter and connective tissue-graft perimeter will be calculated as a percentage of the total graft perimeter [19].

#### Follow-up assessment

All study participants will undergo CBCT at 6 (immediately before implant placement) and 12 months (immediately before crown placement) after the MSFE procedure to assess the outcome. A VAS will be distributed to each participant at 6 and 12 months after surgery to evaluate the oral function over the whole restoration period.

Six months after implant placement (12 months after MSFE), crowns will be placed, which will be designated as the starting point of the 5-year follow-up period. Patients will be called back for re-visits at 18, 24, 30, 36, 42, 48, 54, 60, 66, and 72 months after MSFE to document the implant survival rate, mucosa conditions, and complications. Periapical radiographs will be obtained to survey marginal bone levels, and CBCT analysis will be conducted to observe changes in alveolar bone volume during every visit.

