The reliability and the safety of extended MSFE to the apical area of the neighboring teeth, as proposed by Beitlitum et al. [16], were assessed in a recent clinical trial involving 65 patients to enable future implant placement while avoiding the need for sinus reentry after extraction of the proximal teeth. It can be inferred that MSFE can be successfully achieved prior to extraction of the corresponding teeth.

Base on the dilemma of patients with severe periodontitis and the inference above, the current research proposes MSFE before extraction. In clinical practice, we try to maintain the compromised tooth to fully utilize its residual function in order to reduce the dentition-impaired period by at least 6 months. The extraction and implantation will be completed in one visit to minimize the number of surgeries. This time is a good opportunity to investigate the promoting effect of functional stimulation on bone regeneration, which may improve conditions for implantation.

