### MSFE

For the test group, with the exception of a few specific changes, the surgical procedure will largely mirror the method reported by Tatum [18]. The sinus elevation procedure will be performed before the extraction of the compromised tooth/teeth. Prior to surgery, the compromised teeth will be treated to eliminate inflammation of the periodontal tissue. Once the periodontal status of the compromised teeth is deemed clinically healthy (plaque index ≤ 1; no further bleeding on probing; probe depth≤ 4 mm), a crevicular incision will be made, which is designed to be extended to at least one adjacent tooth both mesially and distally. A full-thickness access flap will be prepared, and an access window (5 × 8 mm) will be created on the lateral wall of the maxillary sinus with the use of a round diamond bur under irrigation with sterile saline. The lower border of the window will be at least 3–5 mm above the floor to maintain an appropriate distance from the teeth on the site. The sinus membrane will be raised by at least 10 mm, exceeding the apical range of the tooth (both buccolingually and mesiodistally). The generated cavity within the maxillary sinus will be filled with deproteinized bovine bone mineral (Bio-Oss®). After the bone substitute is placed, an absorbable collagen membrane (Bio-Gide®; Geistlich Pharma AG) will be placed to cover the antrostomy defect. Interrupted or mattress PROLENE monofilament non-absorbable sutures (Ethicon, Inc., Johnson & Johnson International, Bridgewater, NJ, USA) will be placed to close the primary flap. All patients will receive preoperative antibiotic prophylaxis, consisting of 500 mg of amoxicillin three times daily for 7 days postoperatively. After a healing period of 6 months (prior to dental implant placement), CBCT will be performed to assess vertical bone height at the planned dental implant sites.

For the control group, the procedure will be performed 3 months after the extraction of the compromised teeth/tooth. Besides, standard MSFE will be conducted in accordance with the method described by Tatum [18].

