#### Secondary parameters

The secondary parameters of this study include the following:
The marginal bone level: The marginal bone level will be observed on periapical images obtained with the paralleling technique. Measurements of the mesial and distal bone crest levels adjacent to each implant will be made to the nearest 0.01 mm. The distance between the coronal margin of the implant collar and the most coronal point of the bone-to-implant contact will be recorded. If the margin is above the implant-abutment junction, the distance between the collar and the highest bone level will be recorded. Implants with bone up to the coronal margin of the implant collar will be given a score of zero. The average mesial and distal measurements will be calculated to indicate the stability of the marginal bone [21].The alveolar bone height: The measurements of bone height will be performed by CBCT analysis. CBCT analysis will be conducted using the Mimics Three-dimensional Medical Image Processing Software (version 18.0; Materialise, Leuven, Belgium). Bone height at the implantation site will be measured at three points on the sagittal plane (the middle of insert placement, 2 mm mesial and 2 mm distal). The average of the measurements at these three points will be regarded as the volume of alveolar bone.The surgical duration of the MSFE procedure, which will be calculated from the time of the initial incision to the end of wound closure.Complications during and after the surgery, including infection, hematoma, nasal bleeding, benign paroxysmal positional vertigo, hemorrhage, Schneider’s membrane perforation, infection (especially at the grafting site), sinusitis, and other potential risks that cannot be anticipated before the intervention.Patient-reported outcomes (VAS): Intra- and postoperative discomfort (pain and edema) as well as restoration period discomfort (oral function) will be assessed by applying a VAS. Patients will be asked to rate intraoperative discomfort and postoperative pain levels using a 100-mm scale with “very dissatisfied” on the left and “very satisfied” on the right [22, 23].Histological evaluation of the biopsy sample from the implant site: Histological evaluation will be conducted as previously explained. For each biopsy, the bone volume, graft volume, osteoid volume, connective tissue volume, osteoid-graft perimeter, connective tissue-graft perimeter, and graft perimeter will be calculated.The condition of the mucosa around the implant will be assessed according to the following parameters: probing depth, sulcus bleeding (bleeding index), plaque around the restorations (modified plaque index), and keratinized mucosa width. The occurrence of biological complications (peri-implantitis and peri-implant mucositis) will be recorded.

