## Discussion

As previously reported [16], MSFE before tooth extraction is both safe and reliable. However, the effectiveness of this procedure to reduce discomfort remains uncertain, especially when both sides of molars are periodontally compromised and must be extracted.

In order to reduce the number of procedures, implantation is performed immediately after the MSFE procedure. At the same time, maintaining the tooth will minimize discomfort caused by defective oral function for a period of 3–4 months. We propose that this new clinical strategy will improve patient satisfaction with the procedure.

Because the loss of available bone volume is caused by resorption of the alveolar bone and pneumatization of the sinus mainly due to the loss of functional stimulation of the teeth [24], we presumed that functional stimuli will be beneficial to the outcomes of floor augmentation, both radiographically and histologically. The extent of osteogenesis will also be compared to determine whether the hypotheses will be accepted.

The results of the present study will determine if the modified MSFE procedure, including indications, detailed methods, postoperational complications, and management, is actually beneficial.

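### As stated, oral function is scored and surgery timed only from the sinus lift onwards, so the control side's separate extraction and first 3 toothless months are unmeasured or rest on undefined recall

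*Protocol article*

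**What the plan says.** All references are to the protocol article.

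- **Order of treatment (MSFE; Implant placement).** On the control side "the procedure will be performed 3 months after the extraction of the compromised teeth/tooth". On the test side "The sinus elevation procedure will be performed before the extraction of the compromised tooth/teeth", and the tooth is removed at implant surgery, 6 months after MSFE.
- **Intended benefit (Background).** The compromised tooth is kept "in order to reduce the dentition-impaired period by at least 6 months". A second saving is claimed: "The extraction and implantation will be completed in one visit to minimize the number of surgeries". Objective and hypothesis makes better mastication part of the primary hypothesis. The Discussion sizes the functional gain differently: "minimize discomfort caused by defective oral function for a period of 3–4 months".
- **Oral function (Follow-up assessment).** The VAS is given "at 6 and 12 months after surgery to evaluate the oral function over the whole restoration period". The sentence before it counts 6 and 12 months from MSFE.
- **Discomfort (Baseline assessment).** Pain and edema are scored "immediately and 2 weeks after surgery using a visual analog scale (VAS", in a paragraph that opens with the MSFE operation.
- **Duration (Secondary parameters).** The outcome is "The surgical duration of the MSFE procedure, which will be calculated from the time of the initial incision to the end of wound closure".

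**The concern.** The case for the modified strategy is that the patient keeps a working molar for longer and has one operation fewer. Both gains begin before the control side's sinus lift, because the control tooth is already out by then. The stated patient-burden measures begin at the lift. A burden that only the control side carries is therefore left out of the comparison, or enters it only through a patient's memory over a period the plan does not define.

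What is at stake is the functional half of the primary hypothesis and the claim about the number of surgeries. Discomfort at extraction and function in the weeks after it cannot be recovered at analysis if they were not recorded at the time. The primary parameter, 5-year implant survival, is not affected.

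**Working it through.** **Inputs, with each side's own MSFE as month 0**

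- Control extraction: month -3 (MSFE section).
- Test extraction: month 6, at implant surgery (Implant placement).
- Crown: month 6 + 4 + 1 = 11 (Implant placement), or month 12 (Follow-up assessment). Both are carried through.
- Oral-function VAS: months 6 and 12, reading surgery as MSFE.

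**Step 1. The plan's own figure.** Counting only from MSFE, the control side is toothless from 0 to the crown and the test side from 6 to the crown. The difference is 6 - 0 = 6 months, which agrees with the Background's figure of at least 6.

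**Step 2. Counting from extraction.** Toothless time = crown month - extraction month.

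- Crown at month 11: control 11 - (-3) = 14; test 11 - 6 = 5; difference 9 months.
- Crown at month 12: control 12 - (-3) = 15; test 12 - 6 = 6; difference 9 months.

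The difference is 9 months on either crown date, which also satisfies at least 6. The Discussion's 3 to 4 months matches neither 6 nor 9.

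**Step 3. How much lies before the first stated measure.** Months -3 to 0 make up 3/9 = 33% of the difference, and 3/15 = 20% to 3/14 = 21% of the control side's toothless time. The other 6 months of contrast fall after MSFE.

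**Step 4. What each VAS time can show.**

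- *Before extraction, and months -3 to 0:* no score is stated in the text.
- *Month 6:* the control side has been toothless for 3 + 6 = 9 months, while the test tooth is in place until implant surgery. This is a real contrast if the form is completed before that surgery. The 6-month CBCT is explicitly placed before it; the VAS is not.
- *Month 12:* both sides are toothless if crowns are still pending, or both are crowned if crowns went in at month 11. There is no tooth-present versus tooth-absent contrast either way.

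**Step 5. Surgical episodes.** Control: extraction, MSFE, implant, second stage = 4. Test: MSFE, extraction with implant, second stage = 3. Duration is timed for MSFE only, so for 1 of 4 and 1 of 3. Neither the control extraction nor the combined test visit, where the saving is said to arise, is timed.

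**The case against.** The strongest reply is that the main contrast is measured. Two thirds of it (6 of 9 months) lies after MSFE, and the month-6 score falls at the end of that stretch. A reader might infer that the trial cannot show a functional benefit at all; the month-6 comparison is the reason that does not follow. This part of the reply stands.

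A reader might also infer that the early toothless months are never captured. The text does not establish that. The VAS is meant to cover the full restoration course, so a patient could be recalling months -3 to 0, and surgery is not defined for the oral-function or discomfort scores. Only duration is expressly confined to MSFE. The SPIRIT figure, which may list assessments, is not visible here. These points soften the finding. They do not remove it, because recall with no stated period is a weak substitute for a score taken at the time.

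Nor should one conclude that the plan measures only the step at which the test side is expected to do worse. The Challenges section predicts difficulty in keeping the sinus membrane intact. It does not predict longer surgery or more discomfort.

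Other parts of the reply have some force. VAS and duration are secondary parameters, MSFE duration is a coherent technical outcome in its own right, and the planned episode counts follow from the design without measurement. The omitted period would tend to understate a functional benefit, not create a false one. The Background's figure of at least 6 months is compatible with the schedule; only the Discussion's figure conflicts with it.

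**Conclusion.** The point holds as under-measurement and should be corrected. Of a 9-month planned difference in toothless time (14 to 15 months versus 5 to 6), 3 months and one control-only operation precede every stated oral-function, discomfort and duration measure. Of the two oral-function times, only month 6 carries the contrast of interest. Leaving out months -3 to 0 favours the control side, since only that side carries a burden then. For the untimed implant visit the documents do not settle which side would gain.

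This rests on four assumptions: that surgery means MSFE in the VAS sentences; that months are counted from each side's own MSFE; that the VAS is scored per side, as the paired t test in Statistical analysis implies; and that the unseen figures add no earlier score. The article does not support the stronger conclusion that the benefit cannot be shown.

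**What to change.** 1. In Baseline assessment, Follow-up assessment and Secondary parameters, state which operation surgery means and what period each VAS asks about. Require the month-6 oral-function VAS to be completed before implant placement.
2. Add a per-side oral-function VAS before the first study procedure on either side and immediately before MSFE, for patients not yet past those points. Keep the month-6 paired comparison as the main functional contrast for all patients. Treat the average from first extraction to month 6 as supportive only.
3. Record duration and the immediate and 2-week discomfort VAS for the extraction and implant procedures as well as MSFE, and report them per side.
4. Report tooth-absent days per side from the recorded extraction and crown dates. This is possible for every patient, including those already treated.
5. Reconcile the Discussion's 3 to 4 months with the Background's figure and the schedule, and the crown timing in Implant placement with that in Follow-up assessment.

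The cost is an amendment, a few more forms, and start and stop times at procedures that already take place. Treatment does not change. The main limit is timing: this revision is dated August 2020, about 18 months into a 24-month recruitment period (February 2019 to February 2021). The earliest VAS will be missing for patients already past extraction, which is why the average from first extraction cannot be the main comparison.

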#### Primary outcomes of the trial

The primary parameter of the current trial is implant survival rate, which will be calculated as the proportion of retained implants at 5 years of follow-up.

The criteria of survival or failure of an implant were referred to the consensus of the International Congress of Oral Implantologists [20]. The implant will be regarded as failed if any of the following happens: (a) pain on function, (b) mobility, (c) radiographic bone loss > 1/2 length of the implant, (d) uncontrolled exudate, and (e) no longer in the mouth. Otherwise, the implant will be regarded as surviving.

#### Secondary parameters

The secondary parameters of this study include the following:
The marginal bone level: The marginal bone level will be observed on periapical images obtained with the paralleling technique. Measurements of the mesial and distal bone crest levels adjacent to each implant will be made to the nearest 0.01 mm. The distance between the coronal margin of the implant collar and the most coronal point of the bone-to-implant contact will be recorded. If the margin is above the implant-abutment junction, the distance between the collar and the highest bone level will be recorded. Implants with bone up to the coronal margin of the implant collar will be given a score of zero. The average mesial and distal measurements will be calculated to indicate the stability of the marginal bone [21].The alveolar bone height: The measurements of bone height will be performed by CBCT analysis. CBCT analysis will be conducted using the Mimics Three-dimensional Medical Image Processing Software (version 18.0; Materialise, Leuven, Belgium). Bone height at the implantation site will be measured at three points on the sagittal plane (the middle of insert placement, 2 mm mesial and 2 mm distal). The average of the measurements at these three points will be regarded as the volume of alveolar bone.The surgical duration of the MSFE procedure, which will be calculated from the time of the initial incision to the end of wound closure.Complications during and after the surgery, including infection, hematoma, nasal bleeding, benign paroxysmal positional vertigo, hemorrhage, Schneider’s membrane perforation, infection (especially at the grafting site), sinusitis, and other potential risks that cannot be anticipated before the intervention.Patient-reported outcomes (VAS): Intra- and postoperative discomfort (pain and edema) as well as restoration period discomfort (oral function) will be assessed by applying a VAS. Patients will be asked to rate intraoperative discomfort and postoperative pain levels using a 100-mm scale with “very dissatisfied” on the left and “very satisfied” on the right [22, 23].Histological evaluation of the biopsy sample from the implant site: Histological evaluation will be conducted as previously explained. For each biopsy, the bone volume, graft volume, osteoid volume, connective tissue volume, osteoid-graft perimeter, connective tissue-graft perimeter, and graft perimeter will be calculated.The condition of the mucosa around the implant will be assessed according to the following parameters: probing depth, sulcus bleeding (bleeding index), plaque around the restorations (modified plaque index), and keratinized mucosa width. The occurrence of biological complications (peri-implantitis and peri-implant mucositis) will be recorded.

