### Statistical analysis

For continuous data, such as clinical parameters, consistency between the two examiners will be assessed with the intra-class correlation coefficient. For descriptive data, consistency will be assessed using Cohen’s *k* statistic. Descriptive statistics include frequency values (absolute and relative values) and metric data (arithmetic mean, standard deviation, and median). The measured data will be expressed as the mean ± standard deviation or median (quartile spacing) and the enumerated data as percentages. Cox regression and Kaplan-Meier survival analysis will be conducted to evaluate the survival rate of implants. The incidence of complications will be compared using the *χ*^2^ test. The paired-samples *t* test will be applied to evaluate the VAS scores, clinical parameters, degree of marginal bone remodeling, and vertical bone gain of the test and control groups. Histomorphometric measurements of the biopsies of both groups will be compared using the non-parametric Wilcoxon test for paired samples. All statistical analyses will be performed using IBM SPSS Statistics for Windows, version 19.0. (IBM Corporation, Armonk, NY, USA). Two-sided probability (*p*) values of < 0.05 will be considered statistically significant.

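### The pain and discomfort VAS carries satisfaction anchors, and the oral-function VAS is not tied to a side although a paired comparison of sides is planned

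*Protocol article*

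**What the plan says.** All references are to the protocol article.

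- **What the VAS is for.** Secondary parameters: "Intra- and postoperative discomfort (pain and edema) as well as restoration period discomfort (oral function) will be assessed by applying a VAS". Baseline assessment gives the perioperative part: "Patients will be asked to score their discomfort (i.e., pain and edema levels) immediately and 2 weeks after surgery". The abstract and the section Objective and hypothesis also name discomfort as what the VAS assesses.
- **How the scale is anchored.** Secondary parameters: "Patients will be asked to rate intraoperative discomfort and postoperative pain levels using a 100-mm scale with “very dissatisfied” on the left". The right end is labelled very satisfied. This sentence covers intraoperative discomfort and postoperative pain. No anchors are given for edema or oral function.
- **How oral function is collected.** Follow-up assessment: "A VAS will be distributed to each participant at 6 and 12 months after surgery to evaluate the oral function over the whole restoration period". No side is mentioned.
- **How the scores are analysed.** Statistical analysis names a paired t test and gives its scope as follows: "will be applied to evaluate the VAS scores, clinical parameters, degree of marginal bone remodeling, and vertical bone gain of the test and control groups".
- **What depends on it.** Objective and hypothesis states that the modified procedure should match the standard one clinically and also improve mastication.

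**The concern.** There are two separate problems.

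First, the anchors and the construct do not agree. A pain scale should run from no pain to the worst pain. A scale from dissatisfied to satisfied asks how the patient feels about the experience. A patient in pain who is pleased with the treatment can score high, and a pain-free patient who is unhappy with the process can score low. A paired difference on this scale would be reported as a difference in discomfort when it is a difference in satisfaction. A reader who takes a higher score to mean more pain would also get the direction wrong.

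Second, the trial is split-mouth, so the treatments being compared are the two sides of one mouth. A paired test needs a score for each side. The only description of how oral function is collected is at participant level. Improved mastication is part of the stated hypothesis and the practical reason for keeping the tooth, so an oral-function score that cannot be assigned to a side would leave that part of the hypothesis without a between-treatment estimate.

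**Working it through.** The protocol gives no power or effect-size figure for the VAS, so there is nothing to reproduce. The sample size section concerns implant survival. The check is mainly a comparison of sections.

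**Step 1. Construct against anchors**

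| Item | Stated construct | Stated anchors |
|---|---|---|
| Intraoperative | Discomfort | Very dissatisfied to very satisfied |
| Postoperative pain | Pain level | Very dissatisfied to very satisfied |
| Postoperative edema | Edema level | Not stated |
| Restoration period | Oral function | Not stated |

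The mismatch is explicit for the first two rows. For the last two, nothing can be said about what the anchors measure. If the scale is read in millimetres from the left end (the usual convention, not stated), a higher score is a better experience, so test minus control above zero favours the test side.

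**Step 2. Unit of measurement against unit of analysis**

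- Design: the two sides of each patient are randomised; 25 patients, 50 sites.
- Collection: the oral-function VAS goes to each participant, with no side named.
- Analysis: a paired t test of test against control, which uses d = (test-side score) − (control-side score) for each patient.

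If each form has a rating per side, there are up to 25 values of d. If it has one whole-mouth rating, d does not exist and there are 0 pairs. The protocol does not state which applies.

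The side matters most at 6 months. By the sections on MSFE and implant placement, the control tooth was extracted 3 months before that side's MSFE, and the test tooth stays until implant surgery 6 months after MSFE. Six months after its own MSFE, the control side has been without the tooth for 3 + 6 = 9 months, while the test side, just before implant placement, still has it. A rating that names no side describes a mouth in which both treatments are present.

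**Step 3. Is there another measure of mastication?**

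The primary outcome is implant survival. The seven secondary parameters are marginal bone level, alveolar bone height, surgical duration, complications, the VAS, histology and mucosal condition. Only the VAS addresses oral function.

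**Step 4. What side-specific scores would give**

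The detectable standardised within-patient difference, in units of the SD of d, two-sided α = 0.05, normal approximation, is (z for α/2 + z for power) / √n.

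- n = 25, 80% power: (1.960 + 0.842)/5 = 0.56
- n = 25, 90% power: (1.960 + 1.282)/5 = 0.65
- n = 20 (the 20% dropout assumed in the sample size section), 80% power: 2.802/4.472 = 0.63
- n = 20, 90% power: 3.242/4.472 = 0.72

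The comparison is therefore usable for moderate differences once each side has its own score.

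**The case against.** The strongest reply has four parts.

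1. **One score per participant is not stated.** A reader might infer from "A VAS will be distributed to each participant at 6 and 12 months after surgery to evaluate the oral function" that each patient gives a single oral-function score. The sentence describes handing out a form, not how many ratings it holds, and the planned paired test suggests that per-side scores were intended. The layout of a form is also detail that an article may leave to the full protocol. This stands, so 0 pairs is conditional. What remains is that the collection and analysis sections do not fit together as written.

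2. **The scale can still show a difference.** A reader might infer that the instrument cannot show less discomfort on the test side. The documents do not support that. The perioperative ratings are tied to surgery and could be side-specific, and a satisfaction score can differ between sides. It is a poor proxy for pain, not an empty one. Scale direction alone is a matter of coding and labelling.

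3. **Satisfaction is a stated interest.** The Discussion expects better patient satisfaction, and the scale is supported by two citations that cannot be checked here. That justifies keeping the item. It does not turn it into a pain measure, and the same Discussion separately calls the effect on discomfort uncertain.

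4. **Other inferences go too far.** A reader might conclude that pain and edema share one line and cannot be separated, or that chewing moves to the side that keeps its tooth. Neither is in the documents, and the point does not depend on them. If chewing does shift, left and right ratings would still influence each other, which limits how side ratings can be interpreted.

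The VAS is also one of seven secondary parameters, and the primary outcome and sample size rest on implant survival. That limits the importance of the point, but mastication remains in the primary hypothesis.

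**Conclusion.** The concern holds in two limited parts.

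- **Anchors.** This is a stated rule, not an omission: pain and discomfort are to be rated on a satisfaction scale. Any reported difference will be in satisfaction. The numerical bias for pain cannot be derived from the protocol. That a higher score is better assumes scoring from the left end.
- **Oral function.** The rating side is not fixed, and the participant-level description does not match the paired test. The sections must be reconciled. The consequence ranges from none, if each side is rated (up to 25 pairs, about 0.56 SD detectable at 80% power), to loss of the whole comparison (0 pairs), if only a whole-mouth score is taken.

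The change should be made because this is the only listed measure of the mastication claim. The integrity of the implant-survival outcome is not affected.

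**What to change.** 1. Add 100-mm intensity scales for pain and for swelling, anchored from none to worst imaginable, completed for each operated side immediately and 2 weeks after surgery.
2. Keep the existing satisfaction item as a separate outcome, labelled as satisfaction, with its direction stated.
3. State the anchors for oral function, and state that at 6 and 12 months it is rated separately for the left and right side. If it is to stay a whole-mouth rating, report it descriptively with no comparison of treatments.
4. In the statistical analysis section, limit the paired test to side-specific scores.

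**Cost.** The questionnaire becomes slightly longer. The real cost is timing. Recruitment began on 1 February 2019, and this revision is dated 10 August 2020, about 18 months into a planned 24. Scores already collected can be reported only as satisfaction, so the pain comparison will have fewer than 25 pairs. How many fewer is not stated. If, as an assumption, 10 pairs remained, the difference detectable at 80% power would rise from 0.56 to 2.802/√10 = 0.89 SD. Oral function loses less where patients have not yet reached the 6- or 12-month rating.
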